### 2.13. Patient and public involvement

Based on patients’ priorities, experiences, and preferences, professionally trained staff will objectively evaluate the development of the research question, outcome measures, and burden of each intervention, and this process will be supervised by another staff member. Additionally, individual data will not be reported back to the participants. None of the recruited participants has been involved in the study design, drafting of the manuscript, data collection, analysis, and interpretation, nor in any decision related to the publication of the results.

### 2.14. Ethics and dissemination

Before the participants provide written informed consent, the researcher will be responsible for comprehensively introducing the purpose, procedures, and possible benefits and risks. The study protocol has been approved by the Ethics Committee of the First Affiliated Hospital of Nanjing Medical University (No. 2021-SR-024), Geriatric Hospital of Nanjing Medical University (No. 2021-010), and BenQ Hospital of Nanjing Medical University (No. 2021-KL011). Written informed consent will be obtained from all participants. Study results will be disseminated through peer-reviewed publications and academic conferences.

## 3. Discussion

The purpose of this study will be to evaluate the efficacy, safety, and potential mechanism of *Baduanjin* exercise under remote monitoring in patients with moderate-to-severe COPD. In the BROCADE study, a *Baduanjin* group will be compared to a control group and a PR group, to determine whether or not *Baduanjin* exercise has positive and significant effects on lung function, exercise capacity, cross-sectional area of the pectoralis major and subcutaneous fat, health status, mental status, and quality of life in patients with moderate-to-severe COPD. If this trial is successful, we will be able to conclude that *Baduanjin* exercise can help improve prognosis and quality of life, and provide a promising and effective adjuvant therapy program for moderate-to-severe COPD.

COPD is a complex multisystem disease that can lead to impaired lung function and some systemic manifestations, such as peripheral muscle dysfunction or wasting, cachexia, and negative effects on physiology and psychology. Eventually, this disorder can affect daily activities and lead to disability and premature mortality.^[22]^ Although current therapies may temporarily improve symptoms, they have limited effectiveness in preventing the progressive decline of lung function, the progression of the disease, and the frequency of acute exacerbation. There is an urgent need to determine precise treatments. Based on the GOLD categories,^[20]^ COPD severity is classified as mild (FEV_1 _≥ 80% predicted value), moderate (50% ≤ FEV_1 _< 80% predicted value), severe (30% ≤ FEV_1 _< 50% predicted value), and extremely severe (FEV_1 _< 30% predicted value) in clinical practice. Reports suggest that the outcome of exercise PR in mild COPD patients may not be obvious, and extremely severe COPD patients are susceptible to adverse events. Therefore, moderate-to-severe (30% ≤ FEV_1_ < 80% predicted value) COPD patients with athletic ability will be enrolled in our study to explore the efficacy and safety of treatment.

Computed tomography (CT) is the gold standard for morphological evaluation of lung tissue in vivo, and the imaging phenotype of CT is able to quantify morphological changes of emphysema, large airway obstruction, and air trapping in COPD patients.^[23,24]^ Recently, a study concluded that the CT phenotype of airway surface area-to-volume ratio is an imaging biomarker of airway remodeling, which could provide differential information on predominant airway narrowing and loss and reveal respiratory morbidity, decline of lung function, and survival in COPD.^[25]^ Furthermore, other novel values of the CT phenotype in COPD and other lung diseases need to be explored. In our study, the pectoralis major, a breathing-aid muscle, will be assessed as a promising new evaluation indicator of COPD rehabilitation by high-resolution computed tomography based on the algorithm we developed, compared to the cross-sectional area of the pectoralis major and subcutaneous fat. This is a highlight of the present study. Previous studies concluded that loss of skeletal muscle mass or thickness changes are associated with poor prognosis and disease severity in COPD.^[26–29]^ There is no doubt that the mechanisms by which the condition of the pectoralis major contributes to COPD PR will be revealed in the future.

Chronic airway inflammation is identified as a key factor in the pathogenesis of COPD, characterized by an increase in inflammatory cytokines, including IL-6, IL-8, IL-10, tumor necrosis factor-α, and transforming growth factor-β, which play an important role in the occurrence and development of COPD.^[30]^ Of note, neutrophilic inflammation predominates in the COPD airway lumen and wall, and it can even predict the process and outcomes of this disorder.^[31,32]^ Neutrophils are one of the host’s defense lines against pathogen invasion and they act as phagocytes to remove pathogens with the assistance of cytokines and chemotactic agents. Moreover, neutrophils form reticular ultrastructures known as NETs and release various proteins outside of the cell by degranulation, including myeloperoxidase, neutrophil elastase, and Cit-H3.^[33]^ Compared with healthy controls, accumulation of NETs is significantly increased in COPD sputum and serum, and high NET concentrations are positively correlated with the severity and exacerbation of COPD.^[34]^ However, the role of NETs in COPD pathogenesis remains unclear. Focusing on targeted NETs may be a potential treatment strategy for COPD.

Additionally, much attention has been focused on Siglec-9, which is mainly expressed by human neutrophils and monocytes. Zeng et al^[35]^ confirmed that the expression of Siglec-9 was elevated in various tissues, including plasma, resulting in increased production of human alveolar and peripheral blood neutrophils in COPD patients, which is increased in vitro from peripheral blood neutrophils and culture supernatant by lipopolysaccharides, cigarette smoke extract, dexamethasone, and some cytokines.The polymorphism of Siglec-9 is closely related to the COPD exacerbation-prone phenotype, and the Siglec-9 variant rs2075803 G/rs2258983 A haplotype could be a risk factor for the development of emphysema.^[36]^ Interestingly, Siglec-9 binding with specific anti-Siglec-9 monoclonal antibodies or natural anti-Siglec-9 autoantibodies in human intravenous immunoglobulin (IVIg) preparations can induce neutrophil death by apoptosis, and generate reactive oxygen species involved in cell death signals.^[37,38]^ In our recent study, we hypothesized that an efficient treatment against neutrophil-associated inflammation could be developed using Siglec-9 ligands or agonistic antibodies, and Siglec-9 may be a potential therapeutic target for COPD.^[39]^ Therefore, in this study, we will collect samples of the induced sputum and peripheral venous blood of participants to identify inflammatory cells, inflammatory cytokines, and the expression of NETs and Siglec-9 using a variety of molecular biology methods. Furthermore, the presence of neutrophil-related NETs and Siglec-9 inflammatory mechanisms will be investigated in vitro and in vivo in the future.

*Baduanjin* Qigong has been a part of healthcare for thousands of years in China as part of the theory of traditional Chinese medicine, and it involves eight sections of simple and easy-to-learn movements to smooth Qi and blood and regulate the Yin-Yang balance.^[40]^ Previous studies have confirmed that *Baduanjin* is an aerobic exercise that improves respiration by increasing gaseous exchange and vital capacity.^[41]^ Additionally, this exercise could reduce fatigue, anxiety, and depression symptoms in people with physical or mental illnesses, as well as improve sleep quality and muscle strength of the spine and extremities.^[42,43]^
*Baduanjin* intervention showed a significant improvement in the 6MWD results of patients with mild-to-moderate Parkinson’s disease^[44]^; hence, it may be an effective measure for improving limb function. Notably, a recent meta-analysis concluded that *Baduanjin* exercise could improve lung function, exercise capacity, and quality of life in patients with COPD,^[16,17]^ but there is a lack of evidence from high-quality clinical trials to confirm these findings. Therefore, it is reasonable to expect that the *Baduanjin* exercise is suitable for patients with moderate-to-severe COPD who have low exercise tolerance.

Several strengths are associated with our trial, the BROCADE study. First, the results will be reliable and convincing given the objective measurement of the primary and secondary outcomes. Second, we will combine remote monitoring with smart mobile phone rehabilitation software and monitor the participants’ exercise status and the data in real time.^[45]^ At the same time, we will also set up an alarm system for abnormal heart rate to ensure safety. The device has already been successfully tested. Once it is widely adopted, this device may reduce the social and medical burden of COPD. However, a limitation of this study is that exercise coaches cannot be blinded; thus, the assessment results might be affected by subjective bias. Additionally, the generalizability is limited by the fact that the patients come from a single geographical area. Increased efforts will be needed to carry out multicenter RCTs and multi-dimensional comprehensive comparisons in the future.

In summary, this multicenter RCT will evaluate the efficacy, safety, and potential neutrophil-related inflammatory mechanism of *Baduanjin* exercise by remote monitoring of patients with moderate-to-severe COPD. The BROCADE study is ongoing. We hope that the findings of this trial will show that *Baduanjin*, a safe, effective, simple, and operational exercise, is beneficial for the prognosis and quality of life in patients with moderate-to-severe COPD.

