**Conclusion::**

A novel neutrophil-related inflammatory mechanism will potentially be identified. In addition, the study results will provide a safe, effective, simple and operational *Baduanjin* exercise protocol for moderate-to-severe COPD patients aimed at improving prognosis and quality of life.

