### 2.8. Efficacy assessments

The effects of *Baduanjin* exercise, including clinical symptoms, quality of life, activity and endurance, lung function, and respiratory muscle function, will be evaluated in patients with moderate-to-severe COPD and compared with the effects of the control and PR interventions. The primary outcomes will include the 6MWD and the St. George’s Respiratory Questionnaire index. The secondary outcomes will include lung function test results, including FEV_1_, forced volume capacity (FVC), ratio of FEV_1_ to FVC (FEV_1_/FVC%), maximum expiratory flow rate, and maximum ventilation per minute; chest high-resolution computed tomography to compare the cross-sectional area of the pectoralis major and subcutaneous fat; Modified Medical Research Council scale; COPD assessment test questionnaire results; lower extremity muscle strength; and Short-Form 36-item Health Survey for healthy living results.

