### 2.9. Safety assessments

Although *Baduanjin* exercise is non-strenuous, easy to learn and practice, and unlikely to cause injury,^[21]^ we will evaluate its safety. During the process of exercise intervention, we will monitor the heart rate, finger pulse oxygen saturation, and adverse events (such as dyspnea, dizziness, falls, muscle strain, or COPD exacerbation) of each participant in real time. If any of the above events occur, the training will be stopped, and we will provide professional medical care, emergency observation, or hospitalization in severe cases. These events will be treated as reasons for automatic withdrawal from our study to comply with ethical rules. The details of adverse events will be recorded in the case report file and will be reported to the Ethics Committee within 24 hours.

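### The stated conclusion on prognosis has no listed outcome behind it, and the automatic-withdrawal rule ends follow-up for participants with an adverse event such as a COPD exacerbation

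*Protocol article*

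**What the plan says.** Section 3 (Discussion) states that if the trial is successful, "we will be able to conclude that *Baduanjin* exercise can help improve prognosis and quality of life". The abstract's conclusion describes the exercise protocol as "aimed at improving prognosis and quality of life", and the closing paragraph of section 3 hopes for a benefit on prognosis.

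Section 2.8 lists what will be measured:
- "The primary outcomes will include the 6MWD and the St. George’s Respiratory Questionnaire index".
- "The secondary outcomes will include lung function test results", along with "chest high-resolution computed tomography to compare the cross-sectional area of the pectoralis major and subcutaneous fat", the modified MRC dyspnoea scale, and "COPD assessment test questionnaire results; lower extremity muscle strength; and Short-Form 36-item Health Survey for healthy living results".

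Exacerbation is not among these outcomes. It appears in section 2.9, where, during the exercise intervention, the team will monitor "adverse events (such as dyspnea, dizziness, falls, muscle strain, or COPD exacerbation) of each participant in real time". If such an event occurs, training stops, and the article adds: "These events will be treated as reasons for automatic withdrawal from our study to comply with ethical rules".

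Under section 2.1, exercise lasts 12 weeks, follow-up runs 24 weeks, and outcomes are measured at baseline and every 4 weeks. Under section 2.7, the control arm receives education, a brochure and phone calls, and has no training sessions.

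**The concern.** There are two linked problems.

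First, the article says in advance what success would allow it to conclude, and half of that statement concerns something the trial does not measure. A gain in walking distance or questionnaire score would be reported as better prognosis without any data on exacerbation, admission or survival.

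Second, withdrawal is from the study and not only from training. A participant withdrawn at an exacerbation contributes no later walking distance, questionnaire, admission or death. The loss depends on how the participant is doing, and the way events are detected differs by arm. If the exercise arms lose more of their worse-off participants than the control arm does, the remaining exercisers look better for reasons unrelated to the exercise. This affects the primary comparison at week 12 and the later follow-up, and no analysis plan can recover data that were never collected.

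**Working it through.** The article gives no figure on this point to reproduce, so the check is mainly a comparison of texts. A short calculation shows the possible size.

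**1. Conclusion against outcomes.** In section 3, the sentence just before the conclusion lists what the comparison will determine: lung function, exercise capacity, muscle and fat area, health status, mental status and quality of life. Prognosis is not in that list, nor in the aims in sections 1 and 2.1. Both the abstract and section 3 name prognosis alongside quality of life, so it is not a synonym for it. Section 1 describes the burden of COPD as readmission, death and disability, and counts fewer and milder exacerbations among the goals of treatment. Section 2.8 contains no outcome of that kind. Quality of life is covered by the St. George's questionnaire and the SF-36.

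**2. Could a listed outcome stand in for prognosis?** Section 3 cites earlier work relating muscle loss to poor prognosis and neutrophilic inflammation to disease outcome. Both are associations. The article presents no outcome as a validated surrogate and describes the pectoralis measure as a new and promising indicator. A treatment effect on a correlate does not establish an effect on prognosis.

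**3. Who is lost under section 2.9.** The triggers are dyspnoea, dizziness, falls, muscle strain and exacerbation, given as examples. Monitoring is tied to the exercise intervention, and control participants have none. An event is therefore more likely to be seen, and to lead to withdrawal, in an exercise arm. A first exacerbation could still be counted from the case report file, but counting in controls, between sessions and after week 12 is not secured.

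**4. Possible size.** Assumptions, not from the article: a constant rate of 0.5 to 1.0 exacerbations per patient-year, Poisson events, and 50 participants per arm (150 divided equally by three).

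P(at least one event) = 1 − exp(−rate × weeks/52)

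| Rate per year | By week 12 | By week 24 |
|---|---|---|
| 0.5 | 1 − exp(−0.115) = 10.9% | 1 − exp(−0.231) = 20.6% |
| 1.0 | 1 − exp(−0.231) = 20.6% | 1 − exp(−0.462) = 37.0% |

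By week 12 this is 50 × 0.109 = 5.4 to 50 × 0.206 = 10.3 participants per arm. If every such event led to withdrawal, this cause alone would take about half to all of the 20% dropout allowance in section 2.2.

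**5. Could the trial estimate an effect on exacerbations if everyone were followed?** Events per arm over 24 weeks = 50 × rate × 24/52 = 11.5 to 23.1. The 95% confidence limits of a rate ratio lie a factor exp(1.96 × √(2/events)) either side of the estimate: exp(1.96 × √(2/11.5)) = 2.26 and exp(1.96 × √(2/23.1)) = 1.78. With about 50 per arm, exacerbations can be described but hardly compared.

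**The case against.** The strongest reply is that this is only a matter of wording. The sentence is hedged and sits in the Discussion. It is not an objective, hypothesis or success criterion. The abstract's phrase describes what the exercise is meant to do, the closing paragraph expresses a hope, and no part of the design or analysis depends on the word. This is correct as to status. A reader might infer that better prognosis is a formal criterion on which the trial will be judged, and the document does not support that. What remains is that the conclusion is stated in advance, recurs in the abstract and at the end of the article, and has no outcome behind it.

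On withdrawal, a reader might infer that those who remain are simply the participants who did well. That does not follow: dizziness, falls and strain are also triggers, and the article does not say whether an exacerbation between sessions, or in a control participant, leads to withdrawal. Selection toward a better course is the most that can be said.

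It can also be said that the rule is there for ethical reasons and was approved by three committees (section 2.14). That is a reason to leave the stopping of training alone. It is not a reason to stop collecting data from a participant who agrees to be assessed.

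**Conclusion.** The point holds. The conclusion on prognosis goes beyond the listed outcomes, and the links to prognosis cited in section 3 are associations, which do not close the gap. The withdrawal rule adds a real risk of outcome-dependent loss that is unequal between arms, affecting the 12- and 24-week comparisons and any later view of prognosis.

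The direction most to be feared is one favouring the exercise arms over control. The size cannot be fixed from the article. The 11% to 21% by week 12 rests on an assumed rate and should not be read as a forecast of withdrawals. It is an upper bound for exacerbations at those rates, reached only if every event in the 12 weeks triggers the rule. Other triggers would add to the total loss. Nor should it be inferred that adding an exacerbation outcome would rescue the claim: at these numbers a rate ratio would be uncertain by a factor of about 1.8 to 2.3 each way.

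**What to change.** 1. **Wording.** In the abstract's conclusion and in both places in section 3, limit the stated conclusion to exercise capacity, health status and quality of life.
2. **Section 2.9.** Separate stopping training from ending data collection. Participants with an event stay in the scheduled outcome assessments and in the analysis, in the arm to which they were randomised, where they consent. When training stops is left unchanged.
3. **Optional.** If exacerbations and respiratory admissions are reported, do so descriptively and collect them in the same way in all three arms at the scheduled assessments. Do not rely on the phone calls, which section 2.7 describes only for the control arm, because that would build in unequal ascertainment in an open-label trial. The article does not say outright that the 4-weekly assessments continue to week 24, so this needs confirming.

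**Cost.** The stated conclusion becomes more modest, and participants who would otherwise have been withdrawn must be followed. The change to section 2.9 would probably need to go to the three ethics committees. Recruitment is reported for January to June 2021 and the study is ongoing, so data on participants already withdrawn may not be recoverable. Their number and reasons should be reported by arm.
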